## Abstract

**Background:**

Rheumatoid arthritis (RA) is a chronic inflammatory autoimmune disease with the primary clinical symptoms of joint swelling and pain. Early detection of erosion and synovial inflammation at an active stage resulting from RA can prevent damage to the joints and activity restriction. However, there are still many patients who do not respond to these treatments; the development of newer, safer drugs is urgently needed. Compared to Western medicine, Guizhi-Shaoyao-Zhimu decoction has equal or higher efficacy and safety for RA patients. With the widespread use of musculoskeletal ultrasound (MSUS), this technology holds great value for the degree of joint damage in RA patients, guiding the clinical selection of treatments, and assessing of prognosis. Therefore, we designed a double-blinded randomized controlled clinical trial to measure the safety and efficacy of Guizhi-Shaoyao-Zhimu decoction in treating early-stage RA using MSUS.

**Methods:**

This study is a randomized, double-blinded, parallel group, placebo-controlled trial. A total of 152 adult participants with early RA will be enrolled, with balanced treatment allocation (1:1). The experimental intervention will be Guizhi-Shaoyao-Zhimu decoction plus the conventional medicine methotrexate and the control intervention will be placebo plus the conventional drug methotrexate for 3 months. In addition, both groups will receive folic acid during treatment to prevent side effects from methotrexate. The primary outcomes are the erythrocyte sedimentation rate (ESR), C-reactive protein (CRP), hepatic and renal function, visual analog scale, disease activity score in 28 joints, measurement scale for TCM symptoms, and 7-joint ultrasound score.

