**Assessments**							
Blood routine			X	X	X	X	
Urine routines			X			X	
Hepatic and renal function (ALT, AST, AKP, eGFR, Scr, BUN)			X	X	X	X	
TCM symptoms			X	X	X	X	
ESR, CRP			X	X	X	X	
DAS28, VAS			X	X	X	X	
US7			X			X	
sCD14, MMP3, TIMP1			X			X	
Adverse events			X	X	X	X	

A total of 152 participants will be randomized into the control group or the experimental group. Assessors blinded to the randomization will collect data during the intervention period at baseline and at study months 1, 2, and 3. The peripheral blood levels of matrix metalloproteinase 3 (MMP3), matrix metalloprotease 1 (TIMP1), and soluble cluster of differentiation 14 (sCD14) will be detected before and after treatment to explore the biochemical mechanisms of Guizhi-Shaoyao-Zhimu decoction for the treatment of active RA

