##### Outcome variables

The primary outcome of this trial will be recorded at baseline and at weeks 1, 2, and 3.
Laboratory indexes including routine blood examination, ESR, CRP, and hepatic and renal function will be measured.*The visual analog scale (VAS)* [13]. The pain VAS is self-completed by the respondent. Using a ruler, the score is determined by measuring the distance (mm) on the 10–cm line between the “no pain” anchor and the patient’s pain anchor, providing a range of scores from 0 to 100 [14, 15]. A higher score indicates greater pain intensity.*Disease Activity Score in 28 joints-Erythrocyte Sedimentation Rate (DAS28-ESR)*. DAS28-ESR was calculated as 0.56 × √(Tender joint count) + 0.28 × √(Swollen joint count) + 0.7 × ln ESR + 0.014 × VAS-GH [16].*Measurement scale for TCM symptoms*. To facilitate the evaluation of the results, we will use the measurement scale for TCM symptoms recommended by the Guidelines for Clinical Research of Chinese Medicine (New Drug) [12] to score the symptoms of the patients. The scale consists of 4 major symptoms and 7 minor symptoms. Each symptom is graded on 4 levels, ranging from zero, mild, medium, to severe, with corresponding scores of 0, 1, 2, and 3. The total score was calculated by adding up each score in the scale and using these scores to calculate an efficacy indicator (EI) for the evaluation of treatment efficacy.

EI = (Total symptom score at baseline − Total symptom score post-treatment)/Total symptom score at baseline × 100%

The degree of symptom improvement will be presented in four categories ranging from full recovery (EI ≥ 90%), good recovery (90% > EI ≥ 70%), modest recovery (70% > EI ≥ 30%) to no recovery (EI < 30%).
5.*Ultrasonic assessment*. The 7-joint ultrasound score (US7) [17] is used to determine the degree of synovitis, synovial hyperplasia, and bone erosion. This score examines 7 joints (wrist, MCP2, MCP3, PIP2, PIP3, MTP2, and MTP5 joints) of the clinically dominant hand and foot of the patients. The synovitis, tenosynovitis, and bone erosion of each joint will be observed, with the highest score being 94 points according to the following standards.
Synovial thickening is graded on four grades according to no, light, medium, and heavy, and the corresponding scores are 0, 1, 2, and 3.

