### Statistical analysis

An independent statistician will perform statistical analysis according to the statistical analysis plan using SPSS software (version 26; SPSS Inc., Chicago, IL, USA). Continuous variables will be expressed as the mean (standard deviation) if the data are normally distributed; otherwise, they will be expressed as the median (interquartile). Categorical variables will be presented as frequencies (percentages). Baseline analyses will be performed using analysis of variance or nonparametric tests for continuous variables, and chi-squared or Fisher’s exact tests for categorical variables, respectively. Changes from baseline to post-treatment in DAS28, VAS, TCM syndrome scores, and US7 will be analyzed using analysis of covariance with associated 95% confidence intervals. A two-sided *P* value of 0.05 or less is considered statistically significant. Multiple imputation will be used to handle any missing data.

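### At least seven outcomes are declared primary, none is singled out, and the only threshold is 0.05; if any one may count as success, the false-positive risk is about 18.5% for the four outcomes with a stated test (if independent), not 5%

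*Protocol article*

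**What the plan says.** The abstract of the protocol article (Methods) declares the primaries in the plural: "The primary outcomes are the erythrocyte sedimentation rate (ESR), C-reactive protein (CRP), hepatic and renal function, visual analog scale", followed by "disease activity score in 28 joints, measurement scale for TCM symptoms, and 7-joint ultrasound score". That makes seven listed items.

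The section Outcome variables uses the singular: "The primary outcome of this trial will be recorded at baseline and at weeks 1, 2, and 3". It then lists five groups of measures without ranking them. The first group adds routine blood to the laboratory items: "Laboratory indexes including routine blood examination, ESR, CRP, and hepatic and renal function will be measured". The others are pain VAS, DAS28-ESR, the TCM symptom scale and US7.

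The section Statistical analysis names a between-group comparison for four of these: "Changes from baseline to post-treatment in DAS28, VAS, TCM syndrome scores, and US7 will be analyzed using analysis of covariance". It names none for ESR, CRP, or hepatic and renal function. The only decision threshold is: "A two-sided *P* value of 0.05 or less is considered statistically significant". No success rule, testing order or division of alpha is given.

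The section Sample size calculation works from an effective rate of 40% against 64%. It does not say which of the listed outcomes, if any, that rate comes from.

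**The concern.** A primary outcome tells the reader, in advance, which result decides the trial. Here the reader cannot tell. The plan does not say whether one significant primary is enough, whether all must be significant, or whether one of them leads. The sample size does not settle it either, because it rests on a response rate that matches no listed outcome.

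If one significant result is enough, the 5% threshold applies to each test and not to the trial's main claim. The report could then lead with whichever outcome came out best, and the reader could not know how many chances there had been. The list also mixes efficacy measures with liver and kidney values, which the section Safety guarantee and evaluation uses to monitor harm and for which no direction of benefit is stated.

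**Working it through.** **Plan's own figure.** The plan gives no error rate for its set of primaries. The only figure is the per-test threshold, two-sided 0.05, which is 0.025 in the direction of benefit.

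**Inputs.**
- Outcomes with a stated between-group test: k = 4 (Statistical analysis).
- Items listed as primary: k = 7 (Abstract, Methods), counting hepatic and renal function as one.
- Threshold: 0.05 (Statistical analysis).
- Correlation between outcomes: not given. Some positive correlation is built in, because the DAS28-ESR formula contains ln ESR and a patient VAS. Assumption: a common correlation r from 0 to 0.8.
- Decision rule: not given. Assumption: at least one significant primary counts as success.

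**Independent tests, no true effect on any outcome.** The chance of at least one result at P ≤ 0.05 is 1 − (1 − 0.05)^k.
- k = 4: 1 − 0.95^4 = 1 − 0.8145 = 18.5%.
- k = 7: 1 − 0.95^7 = 1 − 0.6983 = 30.2%.

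Counting only results that favour the experimental arm, it is 1 − (1 − 0.025)^k.
- k = 4: 1 − 0.975^4 = 9.6%.
- k = 7: 1 − 0.975^7 = 16.2%.

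**Correlated tests.** These were simulated with 500,000 draws of k standard normal statistics, each √r times a shared term plus √(1 − r) times its own term. A draw counts if any statistic lies beyond ±1.96 (either direction) or above +1.96 (benefit only).

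| Tests | r | Either direction | Benefit only |
|---|---|---|---|
| 4 | 0 | 18.5% | 9.6% |
| 4 | 0.5 | 15.6% | 7.8% |
| 4 | 0.8 | 11.5% | 5.8% |
| 7 | 0 | 30.2% | 16.2% |
| 7 | 0.5 | 22.9% | 11.5% |
| 7 | 0.8 | 14.9% | 7.4% |
| Nominal, 1 test | – | 5% | 2.5% |

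The smallest value in each column is still more than twice nominal: 11.5/5 = 2.3 and 5.8/2.5 = 2.3.

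**If all primaries had to be significant.** Under that rule the error would not be inflated and would not exceed 5%. The document does not state the rule, and it could not be applied as written, since three of the seven items have no stated test.

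**The case against.** The strongest reply is that a statistical analysis plan is still to be written (Data collection and management) and that the analysis will follow it. Alpha allocation, testing order and the models for ESR and CRP are commonly left to such a plan, and their absence from an article is no fault. That stands for the mechanics. It does not cover the choice of primaries, which this document makes itself: it declares seven. A later plan that named a single primary would contradict the published text.

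A second reply is that the article hopes only for preliminary evidence. That tempers the consequence, but the stated aim is to clarify efficacy and safety, and results are to be called significant at 0.05.

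Some stronger readings are tempting, but the documents do not support them:
- A reader might infer that all seven primaries are each tested at 0.05. Only four have a stated between-group test, so the seven-test figures are an upper scenario.
- A reader might split hepatic and renal function into the six values in Table 1 and count twelve tests, giving 1 − 0.95^12 = 46%. No test of those values is specified, and they would not support an efficacy claim.
- A reader might say that ESR is tested twice, alone and inside DAS28-ESR. It has no stated test of its own. The overlap matters here only as a source of correlation.
- A reader might expect a non-significant laboratory comparison to be taken as proof of safety. Nothing in the article says so, and safety has its own section with regular laboratory tests and adverse event review.

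**Conclusion.** The point holds. The document declares at least seven primary outcomes, singles none out, and gives one unadjusted threshold. This is a choice made in the text, not a detail left out of it.

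If any one significant result may count as success, the four outcomes with a stated test carry a false-positive risk of 11.5% to 18.5% for correlations from 0.8 down to 0. Seven would carry about 15% to 30%. For false claims of benefit, with correlations from 0.5 down to 0, the risk is about 8–10% for four and 11.5–16% for seven, against 2.5%. These figures rest on the any-one-counts rule, on an assumed common correlation, and on no true effect on any outcome. A bare range of 18–30% should not be quoted as the trial's error rate, because it depends on the number of tests and the correlation, neither of which the document settles.

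**What to change.** Before unblinding, do one of the following and make the abstract, Outcome variables and Statistical analysis agree.

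1. Name one primary outcome at day 90. Change in DAS28-ESR by ANCOVA, two-sided 0.05, is the best supported option: eligibility is defined by DAS28, disease activity stands in the first objective, and the ANCOVA is already planned. The text does not dictate it, since that objective pairs disease activity with joint ultrasound.
2. Or keep the four ANCOVA outcomes as primaries under a Holm or Hochberg procedure at overall two-sided 0.05. Day 90 suits this option too: by Table 1, US7 is measured only at baseline and day 90.

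In either case, make the remaining efficacy measures, including ESR and CRP, secondary. Move hepatic and renal function and routine blood to safety.

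Restate the sample size for the chosen primary, because 40% against 64% is tied to none of the listed outcomes. The change is therefore not purely one of wording.

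The cost is that the other outcomes lose primary status under the first option, or face a stricter threshold under the second. Under Holm, for example, the smallest P value would be compared with 0.05/4 = 0.0125.

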**Discussion:**

We designed this double-blinded randomized controlled clinical trial to evaluate the efficacy and safety of Guizhi-Shaoyao-Zhimu decoction in RA patients using MSUS. The results of this trial may provide insights into how to improve the clinical symptoms of RA patients and delay further joint destruction. We hope that this trial may provide preliminary evidence of the efficacy of Guizhi-Shaoyao-Zhimu decoction in treating RA patients and that these results aid researchers, practitioners, and patients alike.

**Aim:**

The main aim of the study is to clarify the efficacy and safety of Guizhi-Shaoyao-Zhimu decoction in patients with early RA.

**Trial registration:**

Chinese Clinical Trials Register ChiCTR2000036141. Registered on 21 August 2020 (retroactively registered)

## Background

Rheumatoid arthritis (RA) is a chronic inflammatory autoimmune disease with the primary clinical symptoms of joint swelling and pain. Patients with severe conditions will suffer from bone destruction, joint deformities, and movement disorders. Globally, the incidence of RA is about approximately 0.8%, and the patient’s health and quality of life are greatly affected [1]. The main purpose of RA treatment is to reduce joint pain, prevent further deformation of the joints, and improve patients’ quality of life [2]. When treating RA at an early stage, optimal efficacy can usually be achieved. During this period, treatment can offer long-term benefits that can permanently change the outcome of the disease [3]. Early detection of erosion and synovial inflammation at an active stage resulting from RA can prevent damage to the joints and activity restrictions. On the other hand, it is very important to evaluate whether RA is in an active stage to provide appropriate treatment options, to evaluate of efficacy, and to aid in prognosis. Currently, Western medicine treatments for RA are mainly NSAIDS, glucocorticoids, DMARDS, and biological agents. However, many patients do not respond to these treatments, and thus, the development of newer, safer drugs is urgently needed. The advantages of treating RA with TCM have been gradually revealed, including in the form of the overall management of patients, fewer side effects, obvious efficacy, effective disease control, and improvement in the quality of life of patients. Thus, TCM can fill the gap in Western medicine.

Guizhi-Shaoyao-Zhimu decoction, which was originally from the book “*Synopsis of Golden Chamber*,” is a commonly used prescription. It is mainly composed of ginger, raw ephedra, prepared licorice, fangfeng, white peony root, cassia twig, aconite root, and common anemarrhena rhizome. It has the functions of promoting blood circulation and relieving pain, providing symptom relief for RA patients. Research has shown that compared to Western medicine, Guizhi-Shaoyao-Zhimu decoction has equal or higher efficacy and safety [4]. Other research [5] has shown that Guizhi-Shaoyao-Zhimu decoction has an anti-rheumatic effect on CIA rats. Its possible mechanism may be related to the inhibition of inflammation, suppression of the invasion and migration of synovioblasts, and induction of apoptosis in synovioblasts.

With the widespread use of musculoskeletal ultrasound (MSUS), it holds great value for evaluating of the degree of joint damage in RA patients, guiding the clinical selection of treatments, and assessing of prognosis. Research [6] has shown that MSUS can be used to measure and identify early cartilage lesions in RA patients in both the short and long term. In addition, due to advances in radiology, it has been reported that [7] the synovial blood flow signal cumulative correlation count of an early-stage RA patient has a predictive effect. Synovial blood flow signal accumulation in the joint, RF level, and laboratory indicators of inflammation are regarded as predictors of disease progression.

Therefore, we designed a double-blinded randomized controlled clinical trial to measure the safety and efficacy of Guizhi-Shaoyao-Zhimu decoction in treating early-stage RA.

## Methods

### Objective

The main objectives of this study are as follows: (1) to evaluate the changes of disease activity and joint ultrasound in patients with early RA treated with Guizhi-Shaoyao-Zhimu decoction and (2) to clarify the efficacy and safety of Guizhi-Shaoyao-Zhimu decoction in patients with early RA.

### Sample size calculation

To determine the sample size, we inquired about the previous research contents. The effective rate of methotrexate in the treatment of rheumatoid arthritis was 40% [8], and that of Guizhi-Shaoyao-Zhimu decoction was 64% [9]. If *α* = 0.05 and the test efficacy 1 − *β* = 0.80, then the sample size; thus, *n* = 122, with 61 patients in each treatment group. Considering a 20% dropout rate, the planned sample size for randomization was increased to 152.
$$ {n}_1={n}_2=\frac{{\left[{Z}_{\alpha /2}\sqrt{2p\left(1-p\right)}+{Z}_{\beta}\sqrt{p_1\left(1-{p}_1\right)+{p}_2\left(1-{p}_2\right)}\right]}^2}{{\left({p}_1-{p}_2\right)}^2} $$

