#### Medication method

For the experimental group (Western medicine + Guizhi-Shaoyao-Zhimu decoction), Guizhi-Shaoyao-Zhimu decoction will be taken twice a day (30 g each time). Combined MTX will be taken orally once a week (10~15 mg). Folic acid tablets will be taken orally twice a week (5 mg).

For the control group (Western medicine + TCM placebo), TCM placebo twice a day, 30 g each time. MTX is taken orally 10~15 mg once a week. Folic acid tablets should be taken 5 mg orally twice a week.

Each patient lasted for 3 months.

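### The sample size rests on an undefined binary effective rate, so the stated 80% power belongs to no efficacy analysis described in the protocol article

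*Protocol article*

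**What the plan says.** **Sizing.** Under Sample size calculation, the article compares two proportions: "The effective rate of methotrexate in the treatment of rheumatoid arthritis was 40% [8], and that of Guizhi-Shaoyao-Zhimu decoction was 64% [9". The error rates are "α* = 0.05 and the test efficacy 1 − *β* = 0.80", and the printed formula is the pooled two-proportion formula with the two-sided normal quantile. The result is 61 per group, 122 in total, raised to 152 for 20% dropout. Effective is not defined there or elsewhere in the article.

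**Primary outcomes.** The Abstract (Methods) names ESR, CRP, hepatic and renal function, VAS, DAS28, the TCM symptom scale and US7. Outcome variables gives essentially the same set. Neither list contains a response rate.

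**Recovery categories.** Under Outcome variables, the TCM symptom scale yields an efficacy indicator (EI), the percentage fall from the baseline score, which is intended for evaluating treatment efficacy. "The degree of symptom improvement will be presented in four categories", with cuts at 30%, 70% and 90%.

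**Analysis.** Under Statistical analysis: "Changes from baseline to post-treatment in DAS28, VAS, TCM syndrome scores, and US7 will be analyzed using analysis of covariance". Chi-squared and Fisher's exact tests appear only in the sentence on baseline comparisons. The significance rule is: "A two-sided *P* value of 0.05 or less is considered statistically significant".

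**Arms.** Under Medication method, both arms take methotrexate: "For the experimental group (Western medicine + Guizhi-Shaoyao-Zhimu decoction" on one side, methotrexate plus TCM placebo on the other.

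**The concern.** A sample size statement tells the reader which comparison the trial can resolve, and how well. Here the sizing endpoint, the primary outcomes and the efficacy test are all stated, and the first matches neither of the others. As printed, the 24-point difference cannot be set against any result the article says will be tested.

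Two things are at stake. A null ANCOVA result could be defended as coming from a trial with 80% power, although the article does not show this for any of the four scores. And because the responder is undefined, the threshold could be chosen late. Data collection and management places development of the statistical analysis plan after completion of the study program and the case report forms. EI alone offers three possible cuts.

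The planning rates raise a smaller question. The two figures come from two different references, and the 64% is attributed to the decoction, while the trial tests the decoction added to methotrexate.

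**Working it through.** **1. The plan's own figure**

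Inputs from Sample size calculation: p1 = 0.40, p2 = 0.64, α = 0.05, power 0.80. The test is two-sided, both in the printed formula and under Statistical analysis. Mean proportion p = 0.52.

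n per arm = [z(α/2)·√(2p(1−p)) + z(β)·√(p1(1−p1) + p2(1−p2))]² / (p1−p2)²

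- First term: 1.960 × √0.4992 = 1.960 × 0.7065 = 1.385
- Second term: 0.842 × √(0.2400 + 0.2304) = 0.842 × 0.6859 = 0.577
- n = (1.385 + 0.577)² / 0.24² = 3.850 / 0.0576 = 66.8, so **67 per arm** (134 total), not 61 (122)

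Other versions give 65 (unpooled variance), 67 (arcsine), 75 (two-sided with continuity correction), 53 (one-sided) and 61 (one-sided with continuity correction). Only the last gives 61, and it contradicts the two-sided, uncorrected formula that is printed.

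Power at 61 per arm under the printed formula: (0.24 × √61 − 1.385) / 0.6859 = 0.714, and Φ(0.714) = **76%**.

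Dropout: 122 / 0.8 = 152.5, which agrees with 152 apart from rounding. From 134, it would be 134 / 0.8 = 167.5, so 168.

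**2. Matching the pieces**

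| Element | Stated in the article | Response rate? |
|---|---|---|
| Sizing endpoint | Effective rate, 40% v 64%, undefined | Yes |
| Primary outcomes | Laboratory values, VAS, DAS28, TCM scale, US7 | No |
| EI categories | Four ordered categories from the TCM scale | Not dichotomised, no test named |
| Efficacy test | ANCOVA of change in DAS28, VAS, TCM scores, US7 | No |
| Tests of proportions | Baseline comparisons | Not for efficacy |

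**3. What 61 per arm gives for the planned ANCOVA**

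The article gives no SD or target difference for any continuous outcome, so the result can only be put in SD units of the score. For a two-sided t-test at 0.05 with 80% power and 61 per arm, the detectable difference is d = 0.511. The normal approximation, (1.960 + 0.842) × √(2/61) = 0.507, agrees closely. Baseline adjustment multiplies d by √(1−r²), where r is the correlation between baseline and follow-up (assumed values):

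| r | Factor | Detectable difference |
|---|---|---|
| unadjusted | 1 | 0.51 SD |
| 0.5 | 0.866 | 0.44 SD |
| 0.7 | 0.714 | 0.37 SD |

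The plan states none of these.

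**4. Is power shown to be lost?**

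Suppose the responder were a cut on a normally distributed score with equal SD in both arms. Then 40% v 64% corresponds to z(0.60) + z(0.64) = 0.253 + 0.358 = 0.61 SD. An unadjusted comparison of means with 61 per arm has about 92% power for that difference, against 76% for the binary comparison. So the mismatch does not by itself show an underpowered trial.

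**The case against.** The strongest reply is that EI is the missing link. It comes from a listed primary scale, its stated purpose is to evaluate efficacy, and it sorts patients into recovery categories from which an effective rate could be formed. This stands in part: a categorical efficacy measure does sit within a primary outcome. But the article does not say which cut is effective, does not tie EI to 40% and 64%, and names ANCOVA of change for the TCM scores.

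A second reply is that the statistical analysis plan, not shown here, may define and test a responder. That limits the claim to this article. It does not remove the mismatch between statements the article itself makes.

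A third is that sizing on a binary outcome is conservative when the analysis is continuous. Under the normal model above that is correct. It helps only an outcome that underlies the undefined responder, and the article does not say which outcome that is.

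A reader might infer that the trial is underpowered, or that its results can never be related to the planning difference. The documents support neither. They give no SD or target difference from which a shortfall in the ANCOVA could be calculated, and the normal model shows one way to relate the two scales.

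A reader might also infer that the 64% comes from decoction without methotrexate. That is unproven. Trial design and setting uses the decoction's name alone as shorthand for this trial's own combination arm, and the cited source is not available here. It is a question for the sponsor, not an error.

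**Conclusion.** The sample size paragraph is wrong as written. It attaches 80% power to a comparison of effective rates that is neither defined, nor listed as a primary outcome, nor tested in any efficacy analysis the article describes. The defect is an unsupported power statement.

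Its size depends on which endpoint is meant. For the planned ANCOVA, 61 evaluable per arm has 80% power for 0.51 SD unadjusted, or 0.44 or 0.37 SD at assumed baseline correlations of 0.5 or 0.7. Whether such differences are realistic or worthwhile cannot be judged from the document. For a responder comparison at 40% v 64%, the article's own two-sided formula gives about 76% power at 61 per arm. These figures assume 61 evaluable patients per arm and a single primary test at two-sided 0.05.

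**What to change.** Align endpoint, test and sample size statement before unblinding, in one of two ways.

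- **(a) Continuous primary.** Name one listed continuous outcome that fits the Objective section, for example change in DAS28-ESR at T90d, as the single primary, analysed by the planned ANCOVA. Restate Sample size calculation as the difference detectable with 61 evaluable per arm at 80% power, in SD units as above, with the assumed correlation stated. If the sponsor has an SD, add the difference in score units. This describes what the fixed number can detect; it does not show that the number is enough.
- **(b) Responder primary.** Prespecify the responder definition and its between-group test as the single primary, with the basis for applying 40% and 64% to that definition. Restate the power at 61 per arm as about 76%. Keeping 80% would need 67 per arm, about 168 randomised at 20% dropout.

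In either case, the sponsor should clarify whether the 64% refers to the decoction alone or with methotrexate.

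Cost: a rewritten sample size paragraph and one sentence on the primary analysis. Option (a) needs no further data or patients. Option (b) needs none either if the less favourable power is accepted.

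### The printed sample size formula with its own inputs gives 67 per group (134 evaluable), not 61 (122); at 61 per group the power of that comparison is about 76%, not 80%

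*Protocol article*

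**What the plan says.** The Sample size calculation section of the protocol article takes its two rates from earlier research: "The effective rate of methotrexate in the treatment of rheumatoid arthritis was 40" per cent, and "that of Guizhi-Shaoyao-Zhimu decoction was 64" per cent. It sets alpha at 0.05 and power at 0.80, and prints a formula for two equal groups. That formula uses Z at alpha/2, a variance term in a single p for the null, separate variances for the alternative, and no continuity correction. The stated result is 122 patients, "with 61 patients in each treatment group". The next step reads: "Considering a 20% dropout rate, the planned sample size for randomization was increased to 152".

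The figure of 152 is the trial's enrolment target. The Abstract repeats it ("A total of 152 adult participants with early RA will be enrolled"), as does the text under Table 1. The Trial design and setting section gives 1:1 allocation. The Statistical analysis section fixes the sidedness of testing: "A two-sided *P* value of 0.05 or less is considered statistically significant".

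**The concern.** The section prints the formula and every numerical input to it, so a reader can check the result directly, and it does not come out. The gap is 6 patients per group (12 in total), about 9% of what the formula requires, which is too much for rounding.

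The power claim is at stake. Anyone relying on this section would take the trial to have a 20% chance of missing a true difference of 40% v 64% at the planned evaluable size. By the section's own formula that chance is about 24%. Because 152 is built directly on 122, the error also carries into the headline enrolment figure.

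**Working it through.** **Inputs.** p1 = 0.40, p2 = 0.64, alpha = 0.05 and power = 0.80 (Sample size calculation); two-sided testing (Z at alpha/2 in the formula, and the Statistical analysis section); 1:1 allocation (Trial design and setting). The article does not define p. I take it as the mean of the two rates, (0.40 + 0.64)/2 = 0.52, and vary this below.

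**Step 1. Try to reproduce 61 from the printed formula.**

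n per group = [Z(alpha/2) × √(2p(1−p)) + Z(beta) × √(p1(1−p1) + p2(1−p2))]² / (p1−p2)²

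- √(2 × 0.52 × 0.48) = √0.4992 = 0.70654
- √(0.24 + 0.2304) = √0.4704 = 0.68586
- Numerator: (1.95996 × 0.70654 + 0.84162 × 0.68586)² = (1.3848 + 0.5772)² = 3.8495
- Denominator: 0.24² = 0.0576
- n = 3.8495/0.0576 = 66.83, so **67 per group, 134 in total**

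The stated 61 and 122 are not reproduced.

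**Step 2. Does another reading give 61?**

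| Reading | n per group, unrounded |
|---|---|
| Two-sided, p = 0.52 (as printed) | 66.83 |
| Two-sided, p set to 0.40 | 65.01 |
| Two-sided, p set to 0.64 | 63.18 |
| Two-sided, unpooled variance throughout | 64.10 |
| Two-sided, pooled variance throughout | 68.02 |
| Two-sided, arcsine | 66.69 |
| Two-sided, continuity-corrected | 74.93 |
| One-sided 5%, no correction | 52.53 |
| One-sided 5%, continuity-corrected | 60.57 |

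Only the last row rounds up to 61. It starts from 52.53 and applies the usual correction: n/4 × [1 + √(1 + 4/(n × 0.24))]² = 13.131 × (1 + 1.1477)² = 60.57. It departs from the printed formula twice (alpha/2 and no correction) and from the two-sided level in the Statistical analysis section.

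**Step 3. Power at the planned evaluable size, by the printed formula.**

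Power = Φ[(0.24 × √n − 1.95996 × 0.70654)/0.68586]

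- n = 61: (1.8745 − 1.3848)/0.68586 = 0.714, power **76.2%**
- n = 60.8 (152 less 20%, halved): 76.1%
- n = 67: 80.1%
- n = 76 (all 152 fully observed): 84.9%

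**Step 4. Exact check.** Summing the binomial probabilities of all outcomes significant at two-sided 0.05 gives, for the uncorrected chi-squared test, 78.1% at 61 per group and 79.4% at 67. With continuity correction, power at 61 is 72.3%.

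**Step 5. Dropout.** 122/0.8 = 152.5 and 152 × 0.8 = 121.6, so 152 agrees with 122 to within rounding. From the corrected figure, 134/0.8 = 167.5, so 168 randomised.

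**The case against.** The strongest reply is that little is lost. The 76% is a normal approximation. The exact power of the uncorrected chi-squared test at 61 per group is 78.1%, only about 1.3 points below its value at 67. That stands, and the shortfall should be described as roughly 2 to 4 points, with a false-negative risk of about 22% to 24%. It does not make 61 the result of the printed formula.

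A second reply is that 61 has a recognisable source: the one-sided, continuity-corrected calculation. This may well be how the figure arose, so it would be wrong to say that no standard method yields 61. It would be equally wrong to say that 61 can arise only if 64% was really about 65%: at 65% the printed formula gives 61.44, which rounds up to 62. But if the one-sided corrected method was used, the printed formula and the two-sided level misdescribe it, and the section still has to be corrected.

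A third reply concerns scope. A reader might infer that the trial as it will be analysed has only 76% power. The article does not support that. The Statistical analysis section names analysis of covariance for changes in DAS28, VAS, TCM syndrome scores and US7, with multiple imputation for missing data. Power for those analyses cannot be worked out from the article. Even for the binary comparison, imputation would keep dropouts in the analysis without restoring their full information, so power with 152 randomised lies between about 76% and 85%. The section nevertheless plans on 20% loss and claims 80% at 61 evaluable per group, and that claim is what fails.

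A reader might also fault the rounding of 152.5 down to 152. That is half a patient and not worth raising.

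**Conclusion.** The point holds as an error of calculation in the Sample size calculation section. For 40% v 64%, two-sided alpha 0.05 and 80% power, the printed formula requires 67 per group (134 evaluable, 168 randomised at 20% dropout). The stated 61 per group (122) gives about 76% power by that formula, or about 78% by exact calculation for the uncorrected chi-squared test.

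This rests on p being the mean of the two rates; setting it to either single rate still gives 64 to 66 per group after rounding up. It also rests on the section's own 20% dropout. The conclusion is limited to the two-proportion comparison used to size the trial. It does not show that the planned outcome analyses are underpowered, nor that more patients must be recruited. The loss is modest, but a sample size and a power on which the trial relies are wrong as written.

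**What to change.** Correct the Sample size calculation section. Keep 152 randomised, and state that 122 evaluable patients (61 per group) give about 76% power for 40% v 64% at two-sided 0.05 by the printed formula. Show 67 per group (134 evaluable, 168 randomised at 20% dropout) as what 80% would need. Define p in the formula as the mean of the two rates, if that is what is meant. The formula and the two-sided level can then stay as they are and will agree with the figures.

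No extra patients are needed, and neither the design nor the analysis changes. The cost is a slightly less favourable stated power.
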